#### MRI

MRI examination is to observe the morphology of the facial nerve of the temporal bone and the transverse diameters of the facial nerve mastoid; second, the genu and tympanic segments will be considered as the outcome indicators. The measurements will be performed within day 4 after onset and day 10 after onset. The MRI examination (SIEMENS MAGNETOM Skyra 3.0T MRI Scanner using head matrix coils) protocol for this study sequence is as follows: T1 three-dimensional magnetization-prepared rapid gradient-echo imaging with the following parameters: 256 × 256 mm field of view (FOV), repetition time/echo time (TR/TE) of 2000.00/1.97 ms, 192 sections of 1.0 mm thickness, with a voxel size = 1.0 × 1.0 × 1.0 mm, flip angle 20°, and acquisition time of 4 min, 40 s.

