## Abstract

**Background:**

Previous studies had already reported the efficacy of electroacupuncture treatment for idiopathic facial nerve palsy (IFP) in a recovery phase; however, the initial use of electroacupuncture in the acute phase remains controversial. Hence, in the present study, we will add electroacupuncture intervention based on oral prednisone tablets in the acute phase of IFP and compare the clinical effects with simple oral prednisone tablets. Besides, the prognosis and safety will be evaluated. The present study aims to evaluate the clinical efficacy, prognosis, and safety of electroacupuncture combined with oral prednisone tablets in the acute phase of IFP, using surface electromyography (sEMG) to objectively observe the recovery of facial expression muscle function. In addition, the morphological changes of the facial nerve were observed dynamically by magnetic resonance imaging (MRI) in the acute phase to reveal the effect mechanism of this therapy.

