### Sample size estimation

According to the previous studies [34], the difference between the SFGS score before and after treatment in the oral administration of prednisolone tablets group was 32.3, with a standard deviation of 8.1. The SFGS score before and after treatment for oral administration of prednisolone tablets combined with electroacupuncture intervention group reached up to 38.3, and the standard deviation was recorded 1. Obtained results were compared with the means of two independent samples. This study was a prospective study with two groups and the sample size was 1:1. The sample size was calculated using the formula $$ n=\frac{\left({Z}_{\alpha }+{Z}_{\beta}\right)2\times \left(1+1/k\right){\sigma}^2}{\delta^2} $$, with a test efficiency of 80%, a beta of 0.2, and an alpha of 0.025. The results show that the number of samples in each group was not less than 36. Considering the problem of missing samples or failing to follow-up, the sample size will be increased by 10%. This means that the minimum sample size of each group will be 40 patients. Finally, the total sample size of the two groups should not be less than 80 patients.

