### Statistical analysis

All statistical analysis will be carried out by the professionals using the SPSS (version 22.0) software. The statistical analysts will be unclear about the specific grouping content of the trial. In the present study, we will use a full analysis set (FAS) and per-protocol set (PPS), and the final conclusion will be based on the results of FAS. The full analysis set (FAS) is based on therapeutic intent. Patients who participate in the randomization but only have received 1-time treatment will also be included in the analysis. In the FAS analysis, for patients who do not complete the trial, the main indicators missed will be derived from the last observation carried forward (LOCF). All statistical analysis will be performed by bilateral differential test, with a *P* value < 0.05 considered statistically significant. Continuous variables will be presented as mean ± standard deviation (normally distributed data) or medians and ranges (non-normally distributed data). For the balance of basic values, analysis of variance or chi-square test or rank sum test will be used. For the primary and secondary outcomes, the analysis of variance will be used. If confounding factors may have an impact on the results, then the co-variance analysis will be used. Further, we will repeat measurements of the same outcome index of the same group at different time points. Changes involved in the rates before and after treatment in each group will be measured by the chi-square test or non-parametric test. The paired *t* test will be used to compare the differences between the groups before and after treatment.

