In the design of clinical trials, the selection of appropriate outcome indicators is critical to evaluate the clinical efficacy. Nowadays, most evaluation methods related to facial nerve function of patients mostly rely on neurological function scales and electrophysiological data and cannot easily observe changes in symptoms and condition. Hence, in the present study, we not only used a series of evaluation scales certified by international guidelines, but also used more intuitive detection technologies such as surface electromyography and MRI, which can evaluate the clinical efficacy before and after the treatment. Surface electromyography can more objectively reflect the recovery of the patient’s facial muscle function, whereas MRI can more directly reflect the recovery of facial nerve edema from the morphology. Moreover, we used NRS to evaluate the degree of pain behind or around the ear, although this symptom did not observe in all the patients. However, according to the epidemiological survey on IFP in the early years, the incidence of pain behind or around the ear is 63% [42], which often affects the recovery of the condition. Therefore, we conducted a statistical analysis and analyzed the degree and duration of pain.

However, this study also has few limitations. First, due to the particularity of acupuncture, we could not blind acupuncturists and patients; however, only evaluators and statisticians were blinded as much as possible. Second, the time interval between follow-up visits was too long, with no other follow-up points set due to the limited research funding and time. Part of the reason was related to the patient’s complex compliance problem. Most patients ended the cycle of follow-up observation in advance after meeting the remarkable improvement of acupuncture treatment. Nevertheless, this research will provide reliable evidence of efficacy and safety for the clinical treatment related to IFP.

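### The MRI diameter outcome names no healthy-side reference, and the day-4 scan cannot serve as a clean baseline because acute treatment has generally begun by then

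*Protocol article*

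**What the plan says.** All references are to the protocol article.

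- **Outcome.** The MRI section, under Secondary outcome, states that "transverse diameters of the facial nerve mastoid; second, the genu and tympanic segments will be considered as the outcome indicators". No side-to-side difference, ratio or covariate is named.
- **Images.** A T1 three-dimensional sequence with head coils, a 256 mm field of view and "192 sections of 1.0 mm thickness, with a voxel size = 1.0 × 1.0 × 1.0 mm".
- **Timing.** "The measurements will be performed within day 4 after onset and day 10 after onset". Table 1 agrees and shows no MRI at enrolment.
- **Population and start of treatment.** The inclusion criteria require unilateral onset within 3 days. The Acute phase sections of both groups run treatment from enrolment to day 10 of onset. All facial needling is on the affected side (Tables 2 and 3).
- **Purpose.** The abstract says that "the morphological changes of the facial nerve were observed dynamically by magnetic resonance imaging (MRI) in the acute phase", in order to reveal how the therapy works. The Discussion says "MRI can more directly reflect the recovery of facial nerve edema from the morphology".
- **Analysis.** "For the primary and secondary outcomes, the analysis of variance will be used", with analysis of covariance if confounding is suspected and repeated measurement over time. Nothing is specific to MRI.

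**The concern.** The MRI is the trial's evidence on mechanism. Rationale for the trial design reports a dispute over whether early electroacupuncture worsens nerve oedema, so readers will look to the MRI for a sign of change in either direction. Each obvious contrast has a weakness:

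- **Day-10 diameter alone.** Differences in nerve size between people stay in the error term.
- **Day 4 to day 10 change, or adjustment for day 4.** These remove stable anatomy. But day 4 generally falls after treatment has started, so they can also remove whatever effect is already present.

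The unaffected nerve in the same image is a reference that needling on the affected side should not alter. Prednisone reaches both sides, but both arms receive it. The MRI section makes no mention of this reference. An imprecise null result could then be presented as no effect on oedema, or as no aggravation of it.

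**Working it through.** **The plan's own figure.** None exists for MRI: the article gives no nerve diameter, expected swelling, between-person spread, reading error or power. The only usable number is the group size: "The results show that the number of samples in each group was not less than 36". That figure is for the primary outcome. With SD 8.1, difference 6.0, two-sided alpha 0.025 and 80% power, the normal formula gives 34.6, so 35, and the t-based version gives 36. It is borrowed below as n = 36 per arm.

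**Assumed inputs (not in the article).** Between-person SD s_b of the true diameter 0.3 to 0.5 mm, with 0.1 mm as a low case. Reading SD s_m 0.15 to 0.29 mm; the upper value is whole-voxel rounding, 1/√12 = 0.29 mm. True left-right correlation 0.8. Reading errors independent between sides and scans. Two-sided alpha 0.05, power 80%.

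**Formulas.**
- Detectable difference = k × residual SD, with k = (1.960 + 0.842) × √(2/36) = 0.660.
- Unadjusted day 10: residual variance v = s_b² + s_m².
- Healthy-side covariate: observed r = 0.8 × s_b² / v; residual variance v(1 − r²).
- Day-4 covariate: slope b = s_b² / v; residual variance v(1 − b²).

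**Example.** s_b = 0.3, s_m = 0.29: v = 0.09 + 0.0841 = 0.1741; unadjusted 0.660 × 0.417 = 0.276 mm. r = 0.072 / 0.1741 = 0.414; 1 − r² = 0.829; adjusted 0.276 × √0.829 = 0.251 mm.

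| s_b | s_m | observed r | unadjusted day 10 (mm) | healthy-side covariate (mm) | day-4 covariate (mm) | b |
|---|---|---|---|---|---|---|
| 0.1 | 0.29 | 0.085 | 0.203 | 0.202 | 0.201 | 0.11 |
| 0.3 | 0.15 | 0.640 | 0.221 | 0.170 | 0.133 | 0.80 |
| 0.3 | 0.29 | 0.414 | 0.276 | 0.251 | 0.236 | 0.52 |
| 0.5 | 0.15 | 0.734 | 0.345 | 0.234 | 0.137 | 0.92 |
| 0.5 | 0.29 | 0.599 | 0.382 | 0.306 | 0.253 | 0.75 |

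**What day-4 adjustment estimates.** Let the true arm difference be δ4 at day 4 and δ10 at day 10. The change score estimates δ10 − δ4. The day-4 covariate model estimates δ10 − b·δ4, so for s_b of 0.3 to 0.5 mm it removes 52% to 92% of any effect present by day 4. Its smaller detectable difference therefore applies to a smaller target unless δ4 is zero. The healthy-side model still targets δ10, or δ4 when applied to the day-4 scan.

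**Voxel size.** With an assumed diameter of 0.8 to 2.5 mm and a change of 10% to 50%, the change is 0.08 to 1.25 mm, above one voxel only at the top corner. A group mean is finer than a voxel, however. Whole-voxel rounding gives an SD of 0.29 × √2 = 0.41 mm for a change, and 0.660 × 0.41 = 0.27 mm is then detectable between arms. Partial-volume bias is outside this calculation.

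**The case against.** Several objections are fair.

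- **There is a within-patient reference.** Each patient is scanned twice, and the analysis section allows repeated measures and covariance analysis. In the table, day-4 adjustment is nominally more precise than the healthy side in every row. That stands as arithmetic, but the day-4 scan is not a pre-treatment value, and the objection does not answer that.
- **Silence is not exclusion.** The MRI section does not say that only the affected side is read, and an article may leave reading rules to a fuller document. This limits the point to a reference that is not named in an outcome definition otherwise detailed enough to give the flip angle and section count.
- **All the sizes are assumed.** True. If people differ little and reading error is large (first row of the table), the gain is negligible. The unadjusted side-to-side difference can even be worse than the raw diameter: 0.298 against 0.276 mm with SDs of 0.3 and 0.29. This favours using the healthy side as a covariate.

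A reader might infer that a change smaller than a voxel makes a null result nearly certain, or that anatomical variation swamps the comparison. The documents support neither. About 0.27 mm remains detectable under whole-voxel rounding, randomisation balances anatomy on average, and two scans are available. Nor does the article say that the MRI will settle the aggravation question; it reports the dispute and assigns the MRI to mechanism.

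**Conclusion.** The point holds as a matter of precision and interpretation for a secondary, mechanistic outcome. The outcome is a diameter on 1.0 mm voxels with no named healthy-side reference, and the only earlier scan generally falls after treatment has started. For between-person SDs of 0.3 to 0.5 mm and reading SDs of 0.15 to 0.29 mm, a healthy-side covariate lowers the detectable day-10 difference by 9% (0.276 to 0.251 mm) to 32% (0.345 to 0.234 mm). This assumes 36 per arm and a true left-right correlation of 0.8, and none of the SDs or the correlation comes from the article. The comparison between randomised arms is not biased by anatomy. The primary conclusion on the Sunnybrook score is not affected.

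**What to change.** 1. In the MRI section, add that the same segments are measured on the unaffected side of the same scans. Compare the arms on the affected-side diameter at day 10, and likewise at day 4, with the healthy-side diameter from the same scan as covariate. Any day 4 to day 10 change should be labelled as change after treatment has started.
2. Report the arm difference in millimetres with its confidence interval. Do not present a null result as absence of oedema change or of aggravation unless the interval excludes a change regarded as relevant. Voxel size is not a suitable threshold for a group mean.

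The cost is extra reading time on images already acquired and two or three sentences of text. No new scan is needed. A finer sequence is not requested: the protocol version is dated 14 February 2021 and recruitment ends on 30 April 2021, so a change now would mix resolutions within the trial.

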### Sample size estimation

According to the previous studies [34], the difference between the SFGS score before and after treatment in the oral administration of prednisolone tablets group was 32.3, with a standard deviation of 8.1. The SFGS score before and after treatment for oral administration of prednisolone tablets combined with electroacupuncture intervention group reached up to 38.3, and the standard deviation was recorded 1. Obtained results were compared with the means of two independent samples. This study was a prospective study with two groups and the sample size was 1:1. The sample size was calculated using the formula $$ n=\frac{\left({Z}_{\alpha }+{Z}_{\beta}\right)2\times \left(1+1/k\right){\sigma}^2}{\delta^2} $$, with a test efficiency of 80%, a beta of 0.2, and an alpha of 0.025. The results show that the number of samples in each group was not less than 36. Considering the problem of missing samples or failing to follow-up, the sample size will be increased by 10%. This means that the minimum sample size of each group will be 40 patients. Finally, the total sample size of the two groups should not be less than 80 patients.

### Adverse events and solutions

Once an adverse event appears, the study team should report to the Ethics Committee and the responsible units within 24 h and record the serious adverse events in the original data in detail. Original data include the following: the time of occurrence of the adverse event, symptoms, signs, its occurrence related to the acupuncture treatment or not, and the details of the corresponding treatment. follow-up time, duration of the adverse event, and the combined medication should be recorded in detail so as to analyze the correlation between adverse events and the trial protocol, and then patients should be taken to the relevant departments immediately to accept the necessary treatment. According to the severity of the adverse event or the patient’s personal decision will be left on the researchers whether to suspend the trial or only the patient to withdraw from the trial.

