**Fig. 1 Fig1:**
[figure not shown]
Trial procedure

**Table 1 Tab1:** Schedule of enrollment, intervention, and assessments of this study protocol

	Study period					
	Enrollment	Treatment				Follow-up
Time point	Day 0	Day 4 after the onset	Day 10 after the onset	Day 11 after the onset	Day 30 after the onset	Days 31–45 after the onset

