**Assessment**						
SFGS	●		●		●	●
H-B	●		●		●	
NRS	●		●		●	
FDI	●				●	
MRI		●	●			
sEMG			●		●	
Adverse event	●	●	●		●	

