### Control group

#### Acute phase (from enrollment to day 10 of onset)

Patients in this phase will be given oral administration of prednisolone tablets (25 mg once daily).

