#### Recovery phase (from day 11 to day 30 of onset)

Patients in this phase will stop taking prednisone tablets and will be provided with electroacupuncture therapy in the recovery phase. The exhaustive methods of electroacupuncture intervention are as follows.

The patients will receive acupuncture treatments in the recovery phase for 9 times. The acupoints used in this study are Yangbai (GB14), Yuyao (EX-HN4), Sibai (ST2), Quanliao (SI18), Dicang (ST4), Qianzheng (EX-HN16), and Hegu (LI4). Furthermore, *Ashi* points will be selected around the orbicularis oculi and the orbicularis oris muscle. The acupuncture needles will be inserted horizontally with a depth of 10 mm to elicit the sensation of *Deqi* sensations. The patients will receive electroacupuncture therapy at the Yangbai (GB14) and *Ashi* point around orbicularis oculi muscle and Qianzheng (EX-HN16) and *Ashi* point around the orbicularis oris muscle (20 Hz, sparse waves), and the needles will be kept for 30 min (three times a week). The specific details about the electroacupuncture therapy and the location of *Ashi* points are shown in Fig. 2.

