### Experimental group

#### Acute phase (from enrollment to day 10 of onset)

Based on the method of the control group, patients in this phase will be combined with electroacupuncture intervention. The medicinal method will be as same as that in the control group. The exhaustive methods of electroacupuncture intervention are as follows.

The experimental group will receive acupuncture treatments in the acute phase for at least 6 times. The acupoints used in this phase are Yifeng (SJ17), Tinghui (GB2), Yangbai (GB14), Yuyao (EX-HN4), Sibai (ST2), Quanliao (SI18), Dicang (ST4), and Hegu (LI4) on the affected side. Then, patients will receive electroacupuncture therapy at the Yifeng (SJ17) (negative electrode) and Tinghui (GB2) (positive electrode) (2/10 Hz, Dilatational wave). The needles will be kept for 30 min (once daily except for Sunday).

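### The acute-phase safety comparison is open to unequal ascertainment of short, mild adverse events, because the experimental arm meets staff on about 7 to 11 days up to day 10 and the control arm has 3 listed contacts

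*Protocol article*

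**What the plan says.** The reporting rule in Adverse events and solutions is triggered by the event and not by a visit: "Once an adverse event appears, the study team should report to the Ethics Committee and the responsible units within 24 h". The same section asks for the time of occurrence, the duration and any relation to acupuncture.

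Table 1 has a row headed "Adverse event", marked for both arms at enrolment (day 0), day 4, day 10 and day 30.

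Contact in the acute phase differs by arm:

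- Experimental arm: "The experimental group will receive acupuncture treatments in the acute phase for at least 6 times". The frequency is given as "The needles will be kept for 30 min (once daily except for Sunday".
- Control arm: "Patients in this phase will be given oral administration of prednisolone tablets". No treatment sessions are described before day 11.

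From day 11 both arms follow one schedule: "The patients will receive acupuncture treatments in the recovery phase for 9 times".

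The Background (Rationale for the trial design) names safety of the acute-phase combination as an aim. The Discussion states that patients and acupuncturists are not blinded.

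**The concern.** The arms differ in how often anyone could notice an event, and they differ in exactly the phase where the treatments differ. Both arms take the same tablets in that phase. A brief steroid effect, such as one poor night or a passing stomach upset, has a near-daily chance of being mentioned in one arm and far fewer chances in the other. If session-noted events enter the comparison, equal true rates can appear as an excess with electroacupuncture.

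This matters because the Background presents acute-phase electroacupuncture as disputed, with some reports that it may worsen nerve oedema. With 40 patients per arm, a few extra minor events could change the safety message.

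**Working it through.** **Inputs.** Onset within 3 days at inclusion (inclusion criteria); acute phase to day 10; needling every day but Sunday, minimum six sessions (Experimental group, Table 2); listed control contacts at enrolment, day 4 and day 10 (Table 1). Assumption: the first session falls on the day of enrolment.

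**The plan's own figure.** Counting non-Sunday days from the first session to day 10, over all seven weekday alignments, gives:

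| First session (day after onset) | Sessions to day 10 |
|---|---|
| 0 | 9–10 |
| 1 | 8–9 |
| 2 | 7–8 |
| 3 | 6–7 |
| 4 | 6 |

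The stated minimum of six is reproduced.

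**Contact days.** Adding the scheduled visits that fall on days without a session:

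| Enrolled on day | Experimental | Control |
|---|---|---|
| 0 | 9–11 | 3 |
| 1 | 8–10 | 3 |
| 2 | 8–9 | 3 |
| 3 | 7–8 | 3 |

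The range is 7–11 against 3, a ratio of 7/3 = 2.3 to 11/3 = 3.7.

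**Upper end: one-day events, no recall.** Assume onset is uniform over the D acute-phase days in the study (D = 8 to 11) and that an event is noted only if it is present on a contact day.

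- Control coverage is 3/D: 3/11 = 0.27 to 3/8 = 0.38.
- Experimental coverage, averaged over weekdays, is 1 − (D − 3)/(7D), because only a Sunday that is not a visit day is missed. This gives 1 − 8/77 = 0.90 for D = 11 and 1 − 5/56 = 0.91 for D = 8.
- The ratio is 3.3 for D = 11 and 2.4 for D = 8.

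**Effect of duration, still with no recall.**

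| Duration | Experimental | Control | Ratio |
|---|---|---|---|
| 1 day | 0.90–0.91 | 0.27–0.38 | 2.4–3.3 |
| 2 days | 1.00 | 0.45–0.56 | 1.8–2.2 |
| 3 days | 1.00 | 0.62–0.70 | 1.4–1.6 |
| 5 days | 1.00 | 0.88–0.91 | about 1.1 |

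**Effect of recall, one-day events.** Let r be the share of missed events recalled at the next scheduled visit (an assumption; the documents give no figure). The ratio is [c_E + (1 − c_E)r] / [c_C + (1 − c_C)r]. For D = 10, c_E = 0.90 and c_C = 0.30:

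- r = 0: 0.90/0.30 = 3.0
- r = 0.5: 0.95/0.65 = 1.5
- r = 0.8: 0.98/0.86 = 1.1

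Counting sessions only in the experimental arm (6/7 = 0.857) gives 2.9, 1.4 and 1.1.

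**After the fix.** The acute-phase comparison rests on the same three common contacts in each arm, 3 against 3.

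**The case against.** The strongest reply is that the quoted sentence is mainly a reporting deadline and not a method of eliciting events. The only stated assessment schedule is Table 1, which is the same in both arms. Time of occurrence and duration are recorded, so an event that has ended can still be entered at the next visit. An article also commonly leaves checklist wording and adverse-event tables to the case report form and analysis plan, and Statistical analysis specifies no between-arm test of adverse events. Much of this stands. The missing elicitation wording is not a fault in itself, and recall at the common visits narrows the gap. The unequal contact and the open-ended capture are nevertheless stated here, and no later analysis can recover events that nobody asked about.

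That controls take tablets at home and are seen only three times is an inference from the lack of described sessions. The phone and WeChat contacts under Plans to promote participant retention are a further channel, but they are described as reminders and not as enquiry about adverse events.

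Extra needling events are real. Fainting, bleeding and hematoma, listed under Confidentiality, can arise from needling before day 11 only in the experimental arm. They are treatment effects and must not be removed as an artefact. It is also fair that over-counting harm in the experimental arm is the cautious direction for a safety claim. It would still mislead where the dispute is whether early electroacupuncture does harm.

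A reader might also infer that within-arm rates must shift at day 11 because contact becomes equal. The documents do not support this. Controls stop the tablets and start electroacupuncture on that day, so any change could be a real treatment effect, and no such comparison is planned.

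**Conclusion.** The point holds as a risk. The acute-phase comparison is open to unequal ascertainment of short, mild events, in the direction of a higher count in the experimental arm. A reader might go further and conclude that the comparison is biased two- or three-fold. The documents do not show that: ratios of that size need events of one or two days that are noted only while present, with little or no recall. Over the assumptions examined, the apparent ratio under equal true rates runs from about 1.1 to about 3. Serious or lasting events are little affected, and recovery-phase contact is the same in both arms. Some imbalance is inherent in an open add-on design without sham sessions, so this is a low-cost improvement and does not invalidate the trial.

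**What to change.** - At the existing common visits (days 4, 10 and 30), ask both arms the same standard adverse-event question, covering the whole interval since the last visit.
- Use those answers for the between-arm comparison of events that can occur in both arms.
- Report the acute phase (to day 10) and the recovery phase separately. The recorded time of occurrence already allows this.
- Also give a full table of all events by arm, with needling-related and session-noted events flagged and not removed, so that the harms of the added treatment stay visible.

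The cost is slightly more case report form and table work, and two adverse-event summaries that must be read together. No visits are added. Patients remain unblinded, so the change reduces differential reporting but cannot remove it.

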### Rationale for the use of intervention

Generally, IFP is a kind of self-limiting disease, and the recovery of Bell’s palsy is usually optimistic. However, there are still 10 to 30% of patients who are observed with residual weakness, asymmetry, or else impaired function [5, 8]. Although this disease is not life-threatening, the facial nerve innervates a total of 23 paired muscles as well as the orbicularis oris. Usually, facial expressions play an indispensable role in interpersonal communication. Therefore, the disease may have a more or less significant impact on psychological [9, 10].

The pathogenesis of IFP is still uncertain. There are two possible mechanisms which probably develop this disease. First, the facial nerve itself is damaged. On the one hand, the spasm of the blood vessels related to the local nutrient nerves caused by wind and cold leads to nerve ischemia, edema, and compression. On the other hand, the facial nerve is infected by rheumatism factor or virus. Second, other peripheral factors can also lead to facial nerve injury. The periostitis in the foramina stylomastoideum causes facial nerve compression or blood circulation disorder or facial nerve edema surrounding the medial temporal area. However, insufficient space for nerve expansion in the bone canal may result in compartment syndrome caused by edema, ischemia, and loss of nerve function [11, 12]. In the incipient of pathological changes related to IFP, the main manifestations are edema and demyelination of the facial nerve, while in the terminal stage, they are related to axonal degeneration and nerve atrophy. The most significant parts are the foramina stylomastoideum and facial canal [12].

However, based on the above pathogenesis, facial nerve edema makes the compression state formed in the facial nerve canal and the blood vessels simultaneously. The circulatory disorder caused by compression makes it difficult to achieve superior blood drug concentration when the drug acts on the local target. This ultimately results in the weakening of the anti-edema and anti-inflammatory effects. Currently, facial nerve decompression (FND) has also been suggested with a feasible surgical technique theoretically. However, there is not enough evidence which can prove if FND intervention is beneficial [13–15]. Therefore, timely intervention and resolution of edema for the acute phase are essential to achieve the best therapeutic effect.

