### Outcomes

In order to reduce the bias of experimental results, the following outcomes will be assessed by an independent outcome evaluator. Before the beginning of the trials, we will conduct a training session for the outcome evaluator. Further, we conducted online meetings via Tencent Meeting due to the ongoing COVID-19 pandemic.

The outcome evaluators will be performed at four time points including the baseline, on day 10 after the onset, on day 30 after the onset, and on day 45 after the onset (follow-up period).

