### Plans to promote participant retention and complete follow-up

Participants will be reminded by the study investigators on every consultation time and will received notifications using the phone call and online instant messaging application “WeChat.”

The study team will educate the subjects about the development trend of disease when they enrolled for the study. Furthermore, the study team will provide acupuncture treatment and oral medicine for free. And to ensure that the treatments will be administered consistently, the acupuncturists which will be assigned have at least 5 years of clinical experience in acupuncture practice.

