### Protocol amendments

Participants may request to discontinue participation in the study at any time. In addition, if there are complications that affect the patient’s condition during the treatment, we will modify the intervention.

If the protocol changes during the implementation of the study, researchers will communicate the important protocol modifications (e.g., changes to eligibility criteria), and paper CRFs will be used to record all the first-hand clinical trial data of the subjects. Researchers should ensure recording of the data is timely, complete, accurate, and true.

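### After an adverse event the protocol lets researchers withdraw the patient from the trial rather than from treatment only, so an obtainable day-30 SFGS may be replaced by LOCF

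*Protocol article*

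**What the plan says.** Protocol article, Adverse events and solutions: depending on severity or the patient's own decision, researchers choose "whether to suspend the trial or only the patient to withdraw from the trial". Withdrawal is thus discretionary, but leaving the trial is the only patient-level stopping route named there.

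Statistical analysis: the final conclusion is drawn from the full analysis set (FAS), which keeps patients who had only one treatment. In that set, "for patients who do not complete the trial, the main indicators missed will be derived from the last observation carried forward (LOCF").

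Main outcome indicators: the primary outcome is the SFGS change from baseline to day 30. Outcomes and Table 1 place SFGS at baseline and then "on day 10 after the onset, on day 30 after the onset, and on day 45 after the onset". Before day 30, therefore, only baseline and day 10 can be carried forward.

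Three other places touch on the same situation:

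- Protocol amendments: for complications "during the treatment, we will modify the intervention".
- Confidentiality: fainting, bleeding, hematoma or infection are treated and recorded, and are described as unlikely.
- Plans to promote participant retention and complete follow-up: "Participants will be reminded by the study investigators on every consultation time".

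None of the three says that a patient who has stopped treatment is still assessed.

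**The concern.** Stopping a treatment and leaving a trial are different events. A patient who cannot tolerate more needling can usually still be graded on day 30. If the adverse-event rule is followed as printed, that patient leaves the trial, becomes a non-completer, and gets an imputed primary value where a real one could have been collected.

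The imputed value is a poor substitute in this disease. The Rationale for the use of intervention says "Generally, IFP is a kind of self-limiting disease", so a baseline or day-10 score carried to day 30 tends to understate recovery. The error can also run the other way. The Rationale for the trial design reports a concern that acute electroacupuncture may aggravate nerve edema. If an event did worsen the palsy, a score taken before the harm would conceal it, in a trial that also sets out to judge prognosis and safety.

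The arms are not equally exposed at first. Electroacupuncture before day 11 is given in the experimental arm only, so losses caused by reactions to it in that period fall on one arm.

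**Working it through.** **The plan's own figures.** Sample size estimation gives the inputs: "the difference between the SFGS score before and after treatment in the oral administration of prednisolone tablets group was 32.3" with SD 8.1, and the "combined with electroacupuncture intervention group reached up to 38.3".

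- Planned difference: 38.3 − 32.3 = 6.0.
- With SD 8.1, 80% power and alpha 0.025 taken as two-sided, n = (2.241 + 0.842)² × 2 × 8.1² / 6² ≈ 34.7, so 35 per group. The t-test version gives 36, the stated figure.
- The 10% increase gives 36 / 0.9 = 40 per group, as stated (36 × 1.1 = 39.6 also rounds up to 40).

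So 40 per arm and a difference of 6.0 are sound inputs for what follows.

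**Shift per withdrawn patient.** Let g be the change the patient would have shown at day 30, and f the share of it already present in the carried value. The arm mean moves down by g × (1 − f) / 40.

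| Carried value | g | Shift (points) | Share of 6.0 |
|---|---|---|---|
| Baseline (f = 0) | 32.3 | 32.3/40 = 0.81 | 13% |
| Baseline (f = 0) | 38.3 | 38.3/40 = 0.96 | 16% |
| Day 10 (f = 0.5, assumed) | 32.3 | 0.40 | 7% |
| Day 10 (f = 0.5, assumed) | 38.3 | 0.48 | 8% |

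If the patient would have shown no change from the carried value, the shift is 0. If the palsy would have been worse at day 30 than at the carried visit, the sign reverses and LOCF flatters the arm.

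**Which rows apply to a one-sided loss.**

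- Before day 11 only the experimental arm receives electroacupuncture. A patient withdrawn for a reaction in that period mostly has no SFGS after baseline, so the baseline rows apply.
- A patient with a day-10 value was lost later. From day 11 both arms receive the same electroacupuncture, so losses from reactions at that stage are not one-sided by design. The day-10 rows describe imprecision within an arm and are not evidence of a built-in difference between arms. Their 50% is an assumption; the documents give no day-10 recovery figure.

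**Total effect.** This would need the number of adverse-event withdrawals per arm. The documents do not give it, so no total is computed.

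**The case against.** The strongest reply is that this is a condensed article. Rules for following patients off treatment often sit in the full protocol, and their absence here proves nothing. The adverse-event sentence can be read as loose wording about scope (halt everything, or only this patient) that does not forbid a day-30 assessment. LOCF applies only to missed values, so a score that is collected would be used. Milder responses exist, namely modifying the intervention or treating and recording. Patients who choose to leave the study are outside any fix.

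Much of this stands. Silence alone would not support the point, withdrawal is not automatic, and the group affected is mainly patients whom researchers withdraw. What remains is printed text: trial withdrawal as the named stopping route, and LOCF as its consequence in the analysis that decides the result. The one-treatment rule governs who is analysed, not what is collected, and reminders tied to consultations do not cover someone no longer treated. If the sentence was meant to say stop treatment, it should say so.

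A reader might infer that the primary comparison is seriously biased. Losing 2 of 40 experimental patients to baseline carry-forward, with none lost in control, would cut the expected difference to 6.0 − 2 × 0.96 ≈ 4.1; losing 4 would cut it to about 2.2. The documents do not support such rates, and these scenarios assume that every lost patient would have gained 38.3. Losses in the control arm for other reasons would offset part of the shift. Where the shift does run against the experimental arm, in a superiority trial it is more likely to cost power than to create a false benefit.

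**Conclusion.** The point holds as a cheap improvement. Followed as written, the adverse-event rule can turn an obtainable day-30 SFGS into a carried baseline or day-10 value in the decisive analysis.

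The between-arm effect expected by design is confined to reactions to electroacupuncture before day 11. There, each patient withdrawn shifts the experimental mean by up to 0.81 to 0.96 points (13% to 16% of 6.0). This assumes 40 per arm, baseline carried, and a patient who would otherwise have gained the planned mean change of either arm. The direction is usually downward but is not fixed, because an event that worsened the palsy would be masked. The total is unknown and probably small, given that the protocol expects few such events.

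A reader might also infer that every adverse event ends participation, or that later losses are one-sided too. Neither follows: withdrawal is left to judgement, and from day 11 the two arms have the same treatment.

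**What to change.** In Adverse events and solutions:

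- Replace researcher-decided withdrawal from the trial with stopping or modifying the study treatment.
- State that these patients keep the scheduled SFGS assessments at days 10, 30 and 45 unless they withdraw consent.
- Record the reason for stopping and the date of the last session.

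In Statistical analysis, state that SFGS values collected after treatment has stopped are used in the FAS.

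The cost is a wording amendment and two CRF fields. No visits are added. The small downside is that patients no longer treated must still be asked to attend visits already on the schedule.
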